# Efficacy and safety of carbetocin applied as an intravenous bolus compared to as a short-infusion for caesarean section: study protocol for a randomised controlled trial

**DOI:** 10.1186/s13063-016-1285-5

**Published:** 2016-03-22

**Keywords:** Carbetocin, Mode of administration, Caesarean section, Uterine tone, Haemodynamic stability

## Abstract

**Background:**

The two most commonly used uterotonic drugs in caesarean section are oxytocin and carbetocin, a synthetic oxytocin analogue. Carbetocin has a longer half-life when compared to oxytocin, resulting in a reduced use of additional uterotonics. Oxytocin is known to cause fewer cardiovascular side effects when administered as a short-infusion compared to as an intravenous bolus. Based on these findings, we aim at comparing carbetocin 100 mcg given as a slow intravenous bolus with carbetocin 100 mcg applied as a short-infusion in 100 ml 0.9 % sodium chloride in women undergoing a planned or unplanned caesarean delivery. We hypothesise uterine contraction not to be inferior to a bolus application (primary efficacy endpoint) and greater haemodynamic stability to be achieved after a short-infusion than after a bolus administration, as measured by heart rate and mean arterial blood pressure (primary safety endpoint).

**Methods/Design:**

This is a prospective, double-blind, randomised controlled, investigator-initiated, non-inferiority trial taking place at the University Hospital Basel, Switzerland.

Uterine tone is quantified by manual palpation by the obstetrician using a linear analogue scale from 0 to 100 at 2, 3, 5 and 10 minutes after cord clamping. We will evaluate whether the lower limit of the confidence interval for the difference of the maximal uterine tone within the first 5 minutes after cord clamping between both groups does not include the pre-specified non-inferiority limit of −10. Both haemodynamic secondary endpoints will be analysed using a linear regression model, adjusting for the baseline value and the dosage of vasoactive drug given between cord clamping and 1 minute thereafter, in order to investigate superiority of a short-infusion as compared to a bolus application.

We will follow the extension of CONSORT guidelines for reporting the results of non-inferiority trials.

**Discussion:**

Haemodynamic stability and adequate uterine tone are important outcomes in caesarean sections. The results of this trial may be used to optimise these factors and thereby increase patient safety due to a reduction in cardiovascular side effects.

**Trial registration:**

Clinicaltrials.gov NCT02221531 on 19 August 2014 and www.kofam.ch SNCTP000001197 on 15 November 2014.

## Background

Uterotonic drugs are routinely used after caesarean section (CS) to reduce blood loss and the risk of postpartum haemorrhage (PPH) [1]. PPH is defined as a blood loss of at least 500 ml after vaginal birth and at least 1000 ml after CS and/or the need for blood transfusion within 24 hours after delivery [2, 3] and represents the most important cause of maternal morbidity [4]. As PPH is more common after CS than after vaginal delivery [5] and as the rate of CS is rising, the incidence of PPH is expected to increase accordingly.

The two most commonly used uterotonic drugs after operative delivery are oxytocin and carbetocin, a synthetic oxytocin analogue. Carbetocin has some advantages over oxytocin due its four- to ten-times longer half-life [6], allowing for a single injection. Moreover, a recent meta-analysis showed that carbetocin significantly reduces the use of additional uterotonics as compared to oxytocin, although the risk of severe PPH remains similar [7].

Carbetocin is associated with cardiovascular side effects including hypotension and a compensatory increase in heart rate similar to those of oxytocin [8, 9]. According to randomised trials with oxytocin, the extent of these cardiovascular side effects seems to be dependent on dose [10, 11] and the rate of administration [12]. The manufacturer of oxytocin requires the drug to be given as a short-infusion to maintain cardiovascular stability. In contrast, the manufacturer of carbetocin recommends a bolus injection of carbetocin. Whether carbetocin administration as short-infusion offers the optimal balance between contractile benefit to minimise maternal haemorrhage and reduce cardiovascular side effects is unclear.

In this randomised controlled trial, we aim to investigate whether carbetocin 100 mcg applied as a short-infusion in 100 ml 0.9 % sodium chloride as compared to a bolus injection minimises the cardiovascular side effects (first secondary safety endpoint) without compromising uterine tone (primary efficacy endpoint) in women undergoing a planned or unplanned caesarean delivery.

## Methods/Design

### Study design and setting

This is a prospective, single-centre, randomised, double-dummy, investigator-initiated, non-inferiority trial conducted at the University Hospital Basel, Switzerland. Study recruitment commenced in December 2014 and is expected to last for 16 months. The study was approved by the regional Ethics Committee (Ethikkommission Nordwestschweiz (EKNZ), EKNZ 2014–088, 13 March 2014). The study was registered in a national and an international trial registry (www.kofam.ch SNCTP000001197 and clinicaltrials.gov NCT02221531).

### Randomisation and blinding

Randomisation for a 1:1 allocation of the study treatment is provided through an online-randomiser to ensure allocation concealment. This online-randomiser was integrated into the password-protected database. The randomisation took place immediately before the CS after having controlled the inclusion and exclusion criteria. The randomisation list was generated in Intercooled Stata Version 13.1 (StataCorp, College Station, TX, USA) using variable block sizes between 2 and 8. The list is safely stored in a separate and sealed file, which will only be opened if unblinding becomes necessary. This is considered to be unlikely since the concomitant treatment in case of insufficient uterine tone is independent of the mode of administration of carbetocin.

Subjects are randomised on arrival in the operating theatre to minimise the risk of dropouts after randomisation. To achieve similar numbers, randomisation is stratified for planned or unplanned CS (Fig. 1).

### Selection and withdrawal of participants

#### Recruitment

Participants are identified at their pre-anaesthesia visit and by screening the daily list of patients scheduled for a CS (Fig. 1). The study staff or the anaesthetist in charge informs the patients about all aspects pertaining to participation in the trial and invites them to participate.

#### Informed consent

Eligibility is routinely assessed by the anaesthesia or obstetric team in order to decide whether the patient is competent to provide consent to participate in the study. Written informed consent will be obtained from all participants. Participants are clearly informed that trial participation is voluntary and that they are free to withdraw at any time without effect on subsequent care. Recruitment of study participants by all members of the research team is in line with the guidance for Good Clinical Practice for obtaining consent [13].

#### Inclusion criteria

Healthy women with a singleton pregnancy undergoing a planned or unplanned CS after at least 37 completed weeks of gestation under regional anaesthesia (spinal, epidural or combined spinal-epidural anaesthesia) aged older than 18 years and with signed informed consent are eligible.

#### Exclusion criteria

The following exclusion criteria are being applied: (1) emergency CS, (2) unplanned CS due to fetal distress, (3) maternal comorbidities such as severe cardiovascular disorders including (pre-)eclampsia, kidney or liver disorders, coagulopathies, as well as epilepsy, (4) uterine malformation, (5) fetal malformation, (6) known hypersensitivity to carbetocin or oxytocin, and (7) the inability to read and understand the participant’s information.

### Study procedure

#### Standard care

After arrival of the patient in the operating theatre, the patient is positioned with a left uterine tilt to avoid aorto-caval compression. A fluid co-load of 500 ml hydroxyethyl starch HES 6 % is infused while the patient is monitored with pulse oximeter, electrocardiogram and non-invasive blood pressure cuff around the upper arm. Spinal anaesthesia by single-shot technique using hyperbaric bupivacaine 0.5 % 10 mg, fentanyl 10 mcg and morphine 100 mcg is applied in right lateral position. If an epidural catheter is already in place, 15–20 ml lidocaine 2 % with carbon dioxide and adrenaline 1:200,000 are administered through the catheter after an intrathecal or intravasal displacement has been excluded. After the application of the spinal anaesthesia, the patient is positioned in a left-tilted recumbent position. The CS is performed according to the in-house standard procedure applying the Misgav Ladach method for the laparotomy [14]. Following uterine incision, delivery of the baby and cord clamping, the placenta is delivered by cord traction or manually, if necessary.

#### Study treatment in intervention and control group

After cord clamping, each patient will receive a 1-ml bolus and a short-infusion of 100 ml 0.9 % sodium chloride, one of which contains of carbetocin 100 mcg and the other of placebo (double-dummy technique). The study intervention only contains the mode of administration of carbetocin. An independent study nurse prepares the study medication (1-ml bolus and 100-ml short-infusion with or without carbetocin 100 mcg). The nurse is the only involved person with access to the randomisation results. All syringes and short-infusions will be labelled according to the Good Manufacturing Practice Guidelines with the study number (1–140) being the only differentiating feature between the study drugs.

#### Concomitant treatments

In case of insufficient uterine tone, the patient will be treated according to the current standard of care. There are six options: (1) uterine massage, (2) sulprostone 4–8 mcg/min, (3) 600 mcg misoprostol rectal, (4) oxytocin infusion 20–40 U/2 h, (5) Bakri™ balloon, and (6) surgical (including Tachosil®) or radiological (embolisation) intervention. The choice of one or several of these interventions is according to the severity of uterine atony and at the discretion of the treating obstetrician.

#### Laboratory analyses

Haemoglobin and haematocrit levels are measured preoperatively and 2 days postoperatively in order to estimate the perioperative blood loss taking into account the calculated pregnancy blood volume and the percent blood volume lost [15, 16].

#### Follow-up visit

All participants have a follow-up visit 2 days postoperatively to rule out side effects of carbetocin and to ensure that no further problems have arisen.

#### Data monitoring and stopping rules

The Ethics Committee agreed that monitoring would be performed by the interdisciplinary study team. This team will evaluate the progress of the trial, verify the accuracy and completeness of the case report forms (CRFs), and ensure that all protocol requirements and investigator’s obligations are being fulfilled. The progress of the trial is evaluated every second month. The overall distribution of uterine tone will be assessed after 2 and 8 months in a blinded way, i.e. without considering group allocation. Extreme values are investigated further by reviewing the intraoperative course and by determining reasons for low uterine tone.

### Study objectives

#### Primary (efficacy) endpoint

The primary efficacy endpoint of this trial is the maximum uterine tone within the first 5 minutes after cord clamping assessed by manual palpation, and rated on a linear analogue scale (LAS) from 0 (completely atonic) to 100 (fully contracted), by the obstetrician.

#### First secondary endpoint (or primary safety endpoint)

The haemodynamic parameters (lowest mean arterial pressure and highest heart rate within the first 5 minutes after administration of the study drug) are considered as primary safety endpoints.

#### Further secondary endpoints

Mean change over time of uterine tone measured 2, 3, 5 and 10 minutes after cord clampingMedian dose of as well as number of patients requiring vasoactive drugs during CS: phenylephrine, ephedrine, atropine, nitroglycerine during the time period before cord clamping, between cord clamping until 1 minute after the end of the short-infusion, and between the second measurement and the end of surgeryMean estimated blood loss within the first 48 hours calculated by multiplying the calculated maternal blood volume by the percent of blood volume lost [15]Need for additional uterotonics (type and amount) during or immediately after surgeryTolerability assessment intraoperatively and 2 days postoperatively by monitoring the following side effects of the study drug: ST segment analysis to detect signs of myocardial ischaemia, angina pectoris, facial flushing, headache, nausea and vomitingAdministration of any blood product (i.e. packed red cells, fresh frozen plasma) or coagulation factors such as tranexamic acid or fibrinogen during or immediately after surgeryMedian time and type of placenta removal, i.e. by cord traction or manually

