The haemodynamic secondary outcomes (lowest mean arterial blood pressure and highest heart rate within the first 5 minutes after the administration of the study drug) will be analysed using a linear regression model adjusting for the corresponding baseline value and the amount of vasoactive drug administered during this period. In a further analysis, the course over time of mean arterial pressure and heart rate will be modelled using a GEE model with an exchangeable correlation matrix, using a knot at the average time of the lowest mean arterial pressure adjusted for the dosage of vasopressors administered, in order to compare the trend over time in both groups. Moreover, the change over time in blood pressure and heart rate will be displayed graphically. The incidence of any clinically relevant ST segment changes in both groups will be compared using a chi-squared or a Fisher’s exact test as appropriate. Further secondary endpoints will only be analysed descriptively. The comparison of the calculated blood loss will be adjusted in a linear regression model for whether or not the mother is breastfeeding.

All analyses and graphs will be performed using Intercooled Stata Version 13.1 for Mac (StataCorp, College Station, TX, USA). We will follow the Consolidated Standards of Reporting Trials (CONSORT) statement and its extension for non-inferiority trials for the future report [18, 19].

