### Choice of non-inferiority design

The aim of this trial is to reach greater haemodynamic stability using the slower administration method (primary safety endpoint) while ensuring non-inferiority with regard to the uterine tone (primary efficacy endpoint) and ultimately the risk of elevated blood loss. Since superiority in haemodynamic endpoints can be achieved with fewer patients, we decided to choose as our primary endpoint non-inferiority in uterine tone.

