### Choice of primary endpoint

We consider the choice of the appropriate measurement of our primary endpoint as a main challenge in this trial. The choice of our primary outcome is based on a randomised controlled trial performed by Butwick et al. [11] who also used a LAS ranging from 0 to 10 to assess uterine tone in a similar setting. We expanded the scale from 0 to 100 to avoid the fact that some outcome assessors used decimal places (e.g. 7.5) while others did not. Moreover, manual palpation of the uterus represents the standard method to assess uterine tone in daily clinical practice. To reduce bias, especially when using a subjective primary outcome measurement, we have established and will maintain blinding by using a double-dummy technique for study drug administration in patients and all care providers until the statistical analysis has been performed. We have chosen to abstain from a binary assessment of the uterine tone as it would be too parallel to our secondary outcome variable ‘any additional uterotonics – yes/no’. The objective efficacy outcome of interest would have been intraoperative blood loss. Blood loss during PPH is often estimated visually, but visual assessment has been shown to be imprecise, usually underestimating blood loss particularly concerning larger volumes [21–24]. We have, therefore, decided to choose the uterine tone as our primary outcome variable. We consider blood loss as a secondary endpoint, calculated by taking into account the pre- and postoperative haematocrit and the estimated blood volume of the parturient [15].

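### The stated 48-hour blood-loss calculation gives no correction for red cells transfused before the day-2 sample, so a transfused woman's loss is understated

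*Protocol article*

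**What the plan says.** Three places in the protocol article describe the calculation, and they agree.

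- Further secondary endpoints: mean estimated blood loss over 48 hours is "calculated by multiplying the calculated maternal blood volume by the percent of blood volume lost".
- Laboratory analyses: "Haemoglobin and haematocrit levels are measured preoperatively and 2 days postoperatively in order to estimate the perioperative blood loss".
- Choice of primary endpoint: blood loss is "calculated by taking into account the pre- and postoperative haematocrit and the estimated blood volume of the parturient".

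The Statistical analysis plan section names one adjustment for this outcome: "The comparison of the calculated blood loss will be adjusted in a linear regression model for whether or not the mother is breastfeeding". Administration of blood products is a separate item in the list of secondary endpoints, limited to products given at or directly after the operation. Nothing in the article links that item to the blood-loss value. The formula for the percentage lost is left to cited references, which are not shown.

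**The concern.** A loss derived from the fall in haematocrit assumes that no red cells entered the circulation between the two samples. If packed red cells are given in that interval, the day-2 value rises and the calculated loss falls. A woman who bled heavily and was transfused can then be scored the same as an untransfused woman who bled much less.

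The article itself gives this outcome some weight. It says of palpated tone as primary endpoint: "The objective efficacy outcome of interest would have been intraoperative blood loss". It describes the design as "ensuring non-inferiority with regard to the uterine tone (primary efficacy endpoint) and ultimately the risk of elevated blood loss". It also sets visual estimation aside because that method tends to underestimate large losses. In transfused women the calculated value, as stated, errs in the same direction. If one arm were transfused more, that arm's excess loss would be understated. If that arm were the short-infusion, the error would favour the impression that it is no worse.

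**Working it through.** **The plan's own figures.** The article states no expected value, SD or margin for blood loss, so there is no blood-loss figure to reproduce. The sample size, used below only for precision, does reproduce. With margin 10, SD 20, one-sided 2.5 % and 80 % power, n = 2 × (1.960 + 0.842)² × 20² / 10² = 62.8, so 63 per group. Then 126 / 0.90 = 140.

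**Error in one woman.** Write BV for blood volume, H0 and H2 for the preoperative and day-2 haematocrit, L for the loss and V for the red-cell volume transfused in between. I assume the simple linear form and a restored blood volume on day 2.

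1. Calculated loss = BV × (H0 − H2) / H0.
2. Without transfusion, H2 = H0 × (1 − L/BV), and the calculation returns L.
3. With transfusion, H2 = H0 × (1 − L/BV) + V/BV, and the calculation returns L − V/H0.

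The understatement is V/H0, and BV cancels.

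**Size per unit.** All inputs are assumptions, since the article gives none.

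- 180 ml red cells per unit and H0 0.36: 180 / 0.36 = 500 ml.
- 150 to 200 ml and H0 0.33 to 0.39: from 150 / 0.39 = 385 ml to 200 / 0.33 = 606 ml.
- Assuming instead a rise of 2 to 3 haematocrit points per unit, BV 5 to 6 litres and H0 36 %: from 5000 × 2 / 36 = 278 ml to 6000 × 3 / 36 = 500 ml.

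Together these span roughly 0.3 to 0.6 litres per unit. At 500 ml per unit, a true loss of 2000 ml is scored as 1500 ml after one unit, 1000 ml after two and 0 ml after four.

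**Effect on the comparison.** The bias in the difference is (share transfused in one arm − share in the other) × units × ml per unit. The article puts PPH at about 5 % of caesarean sections, which I take as a rough guide to the upper end of the share transfused. In 140 women, 5 % is 7.

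| Transfused, bolus vs infusion | 2 units each, 500 ml per unit | 4 units each, 500 ml per unit |
|---|---|---|
| 2 % vs 2 % | 0 ml | 0 ml |
| 2 % vs 5 % | 30 ml | 60 ml |
| 2 % vs 10 % | 80 ml | 160 ml |

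In counts, 1 versus 3 of 70 women with two units each gives (2/70) × 2 × 500 = 29 ml. Across 278 to 606 ml per unit, the 2 % versus 5 % case with two units gives 0.03 × 2 × 278 = 17 ml to 0.03 × 2 × 606 = 36 ml.

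**Against the precision.** With 63 per group, the half-width of the 95 % confidence interval for the difference is 1.96 × SD × √(2/63). That is 105 ml for an assumed SD of 300 ml and 175 ml for 500 ml.

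**The case against.** The strongest reply is that this is a condensed article. The derivation is referred to cited methods, and the full protocol and analysis plan are not shown. Any of them may hold a correction, so the document supports saying that none is stated, not that none exists. That limit stands. It does not dispose of the point, because the article lists the inputs of this calculation and an adjustment for the same outcome. Followed as written, it returns a wrong value for a transfused woman.

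Other parts of the reply also stand, and they rule out stronger readings that a reader might infer.

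- **That the non-inferiority conclusion is biased.** It is not. The decision rests on uterine tone, in both the per-protocol and intention-to-treat analyses. Of blood loss the article says "We consider blood loss as a secondary endpoint", and no margin or decision rule is attached to it.
- **That an excess of bleeding would be hidden.** Blood products and additional uterotonics are endpoints of their own. The Background also counts transfusion within 24 hours as PPH, whatever the calculated loss. A difference in transfusion between arms would be visible there.
- **That the heaviest bleeders are mis-scored.** Only women given red cells before the day-2 sample are affected. A heavy bleeder who was not transfused is untouched by this mechanism.

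**Conclusion.** The point holds as a minor defect in how a supportive outcome is derived. As stated, the calculation understates the loss of a transfused woman by roughly 0.3 to 0.6 litres per unit. That range rests on assumed red-cell content or haematocrit rise per unit, assumed preoperative haematocrit, and the linear formula with blood volume restored by day 2.

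The expected bias in the difference between arms is zero if transfusion is equal in both. Otherwise it is probably tens of millilitres, which is within the assumed confidence-interval width; larger values need a marked imbalance or many units per woman. The practical damage is to individual values and to the upper tail, where large losses would be read. The primary analysis, its margin and the sample size are not affected.

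**What to change.** Add one term to the derivation, fixed before unblinding: corrected loss = calculated loss + (red-cell units given before the day-2 sample × red-cell volume per unit) / preoperative haematocrit. Report the comparison with and without the term. If the full protocol or the cited method already contains such a correction, a sentence saying so is enough.

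The cost is small but not nil. The blood-product endpoint covers only the period of surgery and immediately afterwards, and does not say that the number of units is recorded. Units given later, up to the day-2 sample, would have to be retrieved from patient records. A standard red-cell volume per unit must also be assumed and stated. Few women should be involved. Replacing the day-2 value by a haematocrit taken before transfusion is not a workable alternative, because no such sample is scheduled. With 60 % of patients enrolled when the article was submitted, the rule could still be set before the data are analysed.
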